### Models for Predicting Communication Impairment

#### Preselection of Predictive Features

Since the number of streamlines between two cortical regions is averaged, the connectivity matrix is symmetrical with respect to the diagonal, and only the lower triangular matrix will be used for further analyses. For both lesion-based and connectome-based analyses, the feature set will include hundreds to thousands of feature vectors, and such high-dimensional data can cause the “curse of dimensionality.” To reduce the number of potential features introduced into the predictive model, a preselection procedure will be performed to exclude noisy or uninformative predictors from being fed into the prediction model, which can reduce the chance of model overfitting. First, for lesion-based analyses, only gray matter regions that are lesioned in more than 10% of the patients will be entered into the analysis. Second, for the links in the connectome matrix-based analyses, only those that are present in more than 75% of the patients will be entered into the analysis. After the above steps, each subject will have three feature sets: the lesion feature set, connectome feature set, and combination feature set.

#### Development and Validation of Prediction Models

According to previously reported literature, for children with CP, the distribution of their CFCS grades is unbalanced and skewed. None or mild communication impairment (CFCS level I, II, III) in children with CP and PWMLs is more common than in those with severe communication impairment (CFCS level IV, V) (Kristoffersson et al., 2020). Such an imbalance distribution will cause misprediction during the process of predictive model generation (Saethang et al., 2016). Thus, we defined individuals who communicate at CFCS level I (defined as “effective sender and receiver communication with unfamiliar and familiar partners”) as having an absence of communication impairment. Patients with CFCS level I will be classified into the absence of communication impairment group, and those with CFCS levels II, III, IV, and V will be classified into the communication impairment group. In this way, the CFCS grade will be converted to a binary indicator, and our study will focus on identifying whether children with BCP have any communication impairment and improving the efficacy of the predictive model. All the variables will be centered and standardized before being entered into each model, which will be created with machine learning algorithms. In machine learning, the no-free-lunch theorem states that there is no one model (or, more generically, machine learning tool) that will work best for every problem (Wolpert and Macready, 1997). Therefore, several classification algorithms with varying hyperparameters will be evaluated using support vector machine, random forest, logistic regression, and other methods to investigate which algorithm will outperform competing approaches across all settings. The workflow of data processing and communication prediction is outlined in Figure 2. The detailed model building and validation steps are as follows.

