## Introduction

Cerebral palsy (CP) is the most common physical disability in childhood and occurs in 2–3 per 1,000 live births (Patel et al., 2020). Recently, the majority of individuals with CP achieve a life expectancy close to that of the general population. Clinical and research interests now focus on improving the ability of children with CP to perform activities of daily living and socially interact. Communication plays an integral role in people’s daily activities and social participation, yet only a few studies have examined the prevalence and features of communication impairment in children with CP (Mei et al., 2016; Kristoffersson et al., 2020). Communication (receptive and/or expressive language) impairments are common comorbidities in patients with CP, with a prevalence ranging from 46 to 78% (Coleman et al., 2015, 2016; Mei et al., 2016; Kristoffersson et al., 2020). Communication problems result in poor prospects of engagement and social participation in children with CP across a range of activities, including self-development, social functioning, and learning (Pennington et al., 2019; Vaillant et al., 2020). Particularly by the time these children enter school, communication skills greatly impact school readiness, which affects later social and academic success as well as economic and health outcomes (High, 2008).

Language development from birth to 2 years, when brain plasticity is at its greatest, presents multiple opportunities for intervention (Chorna et al., 2017). During this period, language perception (receptive) and production (expressive) are accompanied by the development of cortical areas responsible for improvements in working memory and pattern recognition in the first year and the multiplication of associations between different cortical processing areas in the second year (McMahon et al., 2012). Social interactions and interventions leveraging cortical development and cortical associations between language and motor systems at this critical time represent a promising role in improving long-term language outcomes and social functions (Goldstein et al., 2003; McMahon et al., 2012; Lipscombe et al., 2016; Chorna et al., 2017). Therefore, the key to interventions in these individuals lies in the importance of the early identification of children with CP at high risk for communication impairments (Coleman et al., 2015).

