### Participants

Some investigators have noted that predictors of communication difficulties may differ for the subgroup of children with CP in early life (Pennington et al., 2020). Therefore, we will limit our study participants to those with BCP (associated with more serious complications and a more common prevalence of communication problems) (Geytenbeek et al., 2015) to find reliable prognostic markers for this population. Brain MRI-based classification systems have been widely recommended and used for classifying different types of brain lesions in children with CP, and different neuroimaging methods may reveal the different pathogenic patterns responsible for CP (Ditchfield, 2017; Himmelmann et al., 2017). Among all the types of lesions, PWMLs are the most common neuroimaging finding in this population (Himmelmann and Uvebrant, 2011; Coleman et al., 2016; Himmelmann et al., 2017), and the severity of PWMLs has been shown to be associated with the severity of communication impairment (Geytenbeek et al., 2015; Coleman et al., 2016; Choi et al., 2017). Thus, we will also constrain neuroimaging to children with BCP and PWMLs to reduce the heterogeneity within our study population.

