#### Sample Size

There are no directly available data to assess the relationship between connectome-based features and clinical assessments of children with BCP to predict their communication ability at school entry. The sample size was calculated according to a previous study (Coleman et al., 2016). In that study of children with CP with a total sample size of *n* = 131, the number of children with communication abnormalities was 62 (47.0%). Multiple linear regression showed that lesion type and five semiquantitative indices that reflected the severity of brain lesions were related to the communication assessment score. However, the efficient size f2 cannot be directly calculated because the R2 and residual variance in the multiple regression model were not reported in the study (Coleman et al., 2016). Geytenbeek et al. (2015) used multiple linear regression based on MRI measures to evaluate language comprehension in non-speaking children with severe CP and PWMLs; that study revealed that the R2 of the model was 0.36. Choi et al. (2017) also found significant negative relationships between the severity of PWMLs and expressive language and between the severity of PWMLs and receiving language performance. Although the above results indicate that the MRI measures could be used to adequately predict communication performance in children with CP, we still assumed a lower efficient size for the MRI measures (f2 as 0.10) to ensure a sufficient sample size for an accurate prediction of communication performance in children with CP. Based on previous studies (Geytenbeek et al., 2015; Coleman et al., 2016; Choi et al., 2017), the number of predictors was set as 6. If α = 0.05, 1-β = 0.80, then the study requires enrollment of 143 participants according to the power calculation by G*Power, version 3.1.9 (Faul et al., 2009). According to previous follow-up experience and given a maximum anticipated dropout rate of 20%, a total sample size of 178 children with BCP and PWMLs will be needed.

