Images from four sites (four hospitals) will be randomly partitioned into four equal portions. Approximately three-quarters of these images will be used as a “training cohort,” and the remaining one-quarter of these images will be used as a “test cohort.” In the “training cohort,” the proportion of lesioned voxels in the ROI and the links of the connectome matrix that are not shown difference between absence of communication impairment group and communication impairment group will be excluded, where the significance level is defined as *P* < 0.05 without multiple comparison correction in the two-sample test. The selected features will be used to define models predicting presence or absence of communication impairment in children with BCP. For each prediction model, 10-fold cross-validation (CV) will be used to evaluate the performance. This means that the “training cohort” will be divided into a training (nine folds) and a validation dataset (one fold), leaving 9 of 10 participants in the training dataset and the remaining participants in the testing dataset. For the training cohort, the various hyperparameters within each algorithm will be used to determine the prediction model. Then, the model will be applied to the validation dataset to predict children with the presence or absence of communication impairment (predicted label). The same procedure will be repeated with each of the one-fold participants or the left-out participants in the leave-one-out procedure, serving as the validation dataset for 10 iterations. Thus, each subject will receive a predicted label, and the accuracy of predictive model will be evaluate by comparing predicted labels to true labels of BCP children. The CV step will be repeated 100 times with random cohort designation to select the model with the best prediction accuracy. The whole “training cohort” will be reused in its entirety to retrain the model based on the classification algorithm and hyperparameters of the prior selected model. Then, the retrained model will be used to evaluate the “test cohort,” and the communication performance of every subject of the “test cohort” will be predicted by the model. The final accuracy of the prediction model will be defined by comparing predicted labels to true labels of BCP children in the “test cohort,” The Receiver Operating Characteristic (ROC) curve and the area under curve (AUC) will be calculated to evaluate the predictive ability of built models. A two-sided Hotelling-Williams test (Steiger, 1980) will be used to determine whether the multimodality prediction model is more accurate than any of the single-modality prediction models. *P* values < 0.05 will be considered indicative of statistically significant differences across models. Given the possible effects of age on imaging measures, the “test cohort” will be divided into three groups: younger (6–12 months), middle-aged (12–18 months), and elderly (18–24 months years), according to their age at MRI scan. The optimal model will be applied to all subgroups to exam whether the prediction accuracy changes with age at MRI scan.

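### The balance of the adopted CFCS cut (I versus II-V) is never shown, and choosing models on raw accuracy can favour a weak, low-specificity model if about 70% or more of children are impaired

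*Protocol article*

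**What the plan says.** All places are in the protocol article.

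- **Reason for the cut** (Development and Validation of Prediction Models). The CFCS distribution is described as skewed. The only imbalance named is levels I-III outnumbering IV-V, and no figure is given. The stated consequence is: "Such an imbalance distribution will cause misprediction during the process of predictive model generation". The outcome is then dichotomised as level I (no impairment) against II-V (impairment). The section also says that the aim is to identify any impairment.
- **Selection rule** (same section, text after Figure 2). Accuracy is the agreement of predicted with true labels. Ten-fold cross-validation is repeated 100 times "to select the model with the best prediction accuracy". The chosen algorithm and hyperparameters are refitted on the whole training cohort and carried to the test cohort.
- **Role of ROC and AUC.** They evaluate models already built. The Figure 2 caption applies the ROC curve to the test cohort, then picks the best of three feature-set models without naming the measure.
- **Prevalence.** The Introduction describes receptive and/or expressive language impairment in cerebral palsy "with a prevalence ranging from 46 to 78" per cent. Sample Size cites 62 of 131 (47.0%) from an earlier cohort of children with cerebral palsy. Participants says that bilateral disease is "associated with more serious complications and a more common prevalence of communication problems", without a number.

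**The concern.** The plan treats class imbalance as harmful and moves the cut to avoid it, but shows imbalance only at the cut it rejects. II-V is the widest definition of impairment that the CFCS allows, and Table 1 shows that level II includes children who communicate effectively but more slowly. With the article's remark that bilateral disease carries more communication problems, the new cut could be skewed the other way, to 78:22 at the top of the quoted range.

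Raw accuracy is the measure most exposed to such skew, because giving every child the majority label already scores the majority proportion. A low-specificity model could then be chosen over one that separates the groups better. The study wants to pick out high-risk children before school; a model that calls nearly everyone impaired does not do that.

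**Working it through.** **1. The plan's own figure.** The article gives no class-balance or accuracy figure for I versus II-V, so there is none to reproduce on this point. The sample size supplies the denominator: "If α = 0.05, 1-β = 0.80, then the study requires enrollment of 143 participants". With f² = 0.10 and 6 predictors, the F test of R² = 0 (noncentrality 0.10 × 143 = 14.3; 6 and 136 degrees of freedom) has power 0.801, so 143 reproduces. Three-quarters of 143 is about 107 training children, which leaves 36 for testing.

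**2. Constant rule.** Giving every child the majority label has accuracy max(p, 1 − p), where p is the impaired proportion: 0.54 at p = 0.46, 0.60 at 0.60, 0.70 at 0.70 and 0.78 at 0.78. Its AUC is 0.50 throughout, and for p above one half its specificity is 0.

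**3. Best accuracy of an informative model (assumed form).** Let scores be N(0,1) in unimpaired and N(d,1) in impaired children, with d = √2 × Φ⁻¹(AUC).

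- Accuracy at threshold c is p × Φ(d − c) + (1 − p) × Φ(c).
- It is largest at c = d/2 + ln[(1 − p)/p]/d.

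Example with p = 0.78 and AUC 0.70: d = 0.742 and c = −1.336. Sensitivity is Φ(2.078) = 0.981 and specificity is Φ(−1.336) = 0.091. Accuracy is 0.78 × 0.981 + 0.22 × 0.091 = 0.785.

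| Impaired | Constant rule | AUC 0.60 | AUC 0.70 | AUC 0.80 |
|---|---|---|---|---|
| 46% | 0.54 | 0.578 | 0.648 | 0.726 |
| 60% | 0.60 | 0.611 | 0.664 | 0.735 |
| 70% | 0.70 | 0.700 | 0.720 | 0.769 |
| 78% | 0.78 | 0.780 | 0.785 | 0.812 |

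Specificity at these thresholds for AUC 0.60, 0.70 and 0.80 is 0.01, 0.22 and 0.45 at 70% impaired, and 0.00, 0.09 and 0.32 at 78%.

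**4. Can selection see the difference?** Competing models are scored on the same children, so the paired difference matters. I simulated 107 independent children with the threshold of step 3 taken as known, and counted how often the model strictly beats the constant rule.

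| Impaired | AUC 0.70 | AUC 0.80 | AUC 0.85 |
|---|---|---|---|
| 46% | 96% | >99% | >99% |
| 60% | 88% | 99% | >99% |
| 70% | 69% | 93% | 98% |
| 78% | 51% (ties 21%) | 81% (ties 7%) | 92% |

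At 78%, the AUC 0.70 model gains 0.005 in accuracy against a paired standard error of 0.018. The AUC 0.80 model gains 0.032 against 0.032.

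**5. Same model, balanced threshold.** At sensitivity = specificity, an AUC 0.70 model scores Φ(0.742/2) = 0.645 at every prevalence. At 78% impaired, raw accuracy ranks this below the constant rule's 0.78: the constant rule ties or beats it with probability 0.99 in 107 children (0.83 at 70%, 0.27 at 60%, 0.07 at 46%). Raw accuracy therefore pushes the threshold towards the low-specificity version in step 3.

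**6. Under another criterion.** Balanced accuracy gives the constant rule 0.50 at every prevalence and the model of step 5 0.645. AUC gives 0.50 against 0.70.

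**The case against.** Several points on the other side stand.

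- **The quoted range is not the prevalence of II-V here.** It describes language impairment in cerebral palsy in general. The only prevalence used in planning, 47.0%, is close to an even split and also comes from cerebral palsy in general. The article points upward for bilateral disease but gives no number, so 78:22 is a worst case and not the plan's expectation.
- **Moving the cut is not illogical.** If I-III dominate, shifting II and III to the other side is a reasonable direction, and detecting any impairment is a separate reason for it.
- **AUC is planned.** A model that labels everyone impaired would show a test AUC near 0.50, so it would not pass unnoticed. This limits the harm but does not remove it: by then the algorithm and hyperparameters are fixed, and choosing again would reuse the test cohort.

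A reader might infer that accuracy cannot tell a useful model from a constant label anywhere between 46% and 78%. The figures do not support that. At 46% impaired, an AUC 0.70 model beats the constant rule in about 96% of draws, and even at 78% an AUC 0.80 model does so in about 81%. Nor should the standard error of a single accuracy, √(0.78 × 0.22/107) = 0.040, be used to call the models inseparable; the paired error is smaller.

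The selection criterion is nevertheless a stated rule, not a detail left to a fuller plan.

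**Conclusion.** The point holds in a limited form. The article justifies its cut by imbalance at a different cut, does not show the balance of the one it adopts, and selects models on a measure that is sensitive to that balance.

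The consequence depends on a prevalence that the documents do not give. At about 70% impaired or more, accuracy-based selection can favour a weakly discriminating, low-specificity model. At 78%, going from no discrimination to AUC 0.70 adds only 0.005 to the best attainable accuracy. About 8 of the 36 evaluable test children would then be unimpaired (36 × 0.22 = 7.9), and a specificity of 0.09 would identify fewer than one of them (7.9 × 0.091 = 0.7). Near 46-54% the criterion is workable.

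The sizes rest on an equal-variance binormal score, the AUC values shown, known thresholds and 143 evaluable children. The sample-size calculation is unaffected. This is a change worth making, not a fatal flaw.

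**What to change.** In Development and Validation of Prediction Models, replace best prediction accuracy as the cross-validation criterion with mean cross-validated AUC or log-loss over the 100 repeats; balanced accuracy is an acceptable alternative. Use the same measure to choose among the three feature-set models, where Figure 2 names none. Read test accuracy against the majority-class rate in the test cohort.

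This takes about a sentence in the selection rule, needs no new data, and uses quantities that the plan already computes or can obtain from the same fits. If the classes prove balanced, little is lost. The downside is that the reported accuracy may be slightly lower than under direct selection on accuracy.

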#### Harmonization

Multisite imaging studies are prone to technical variability across scans, including differences between the manufacturers, heterogeneity in the protocol and variations in the scanning parameters. Such unwanted variation can hinder the detection of important features and/or cause spurious findings. There is a need to remove the bias and non-biological variance caused by unwanted site effects. In this study, we will use ComBat (Fortin et al., 2017, 2018), a method that adjusts the mean value and variance between different groups by combining an empirical Bayes framework and the location/scale model, to harmonize the data. Studies have shown that the ComBat method performs well in preserving biological variability and removing the unwanted variation introduced by site for harmonizing the 3DT_1_ imaging (Fortin et al., 2018) and DTI (Fortin et al., 2017).

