**FIGURE 2 F2:**
[figure not shown]
Data processing and analysis workflow. **(A)** First, the lesion will be manually defined on T_2_-FLAIR images. **(B)** Two complementary methods, one based on lesions and the other on the connectome, will be used to characterize brain damage. To compute lesion-based damage (top row), the brain atlas and each individual’s lesion mask will be aligned with each individual’s native T_1_ space. The gray matter regions will be divided into regions of interest (ROIs) according to the atlas. Then, lesion-based damage will be computed as the proportion of lesioned voxels per ROI based on the lesion mask. Connectome-based damage (bottom row) will be computed as the number of diffusion tensor imaging (DTI) tracts that connect each pair of ROIs (tractography for reconstructing tracts will be performed guided by the white matter probabilistic map). **(C)** For each individual, three feature sets (lesion features, connectome features, and combination features) will be generated from the corresponding features after feature selection. **(D)** For each feature set, a “training cohort” will be used to build an optimal model based on a 10-fold cross-validation, and the prediction performance of the optimal model will be tested with the “test cohort” using ROC curve. **(E)** Then, three optimal models will be generated based on different feature sets (the lesion feature set for voxel model, the connectome feature set for connectome model, and the combination feature set for combination model). The prediction performance of each model will be compared, and the best-performing model will be selected.

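### As described, the prevalence filters and ComBat are not confined to the training cohort, so the test cohort is not fully held out; its accuracy can be biased, mainly downward, if impairment rates differ by hospital

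*Protocol article*

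**What the plan says.** Four places in the protocol article bear on this.

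- **Harmonization.** Site effects will be removed with ComBat, "a method that adjusts the mean value and variance between different groups". It is applied to the data without a stated limit to the training cohort. No timing relative to the split and no preserved covariates are given.
- **Preselection of Predictive Features.** Gray matter regions are kept if lesioned in over 10% of the patients, and connectome links if present in over 75% of the patients. Then: "After the above steps, each subject will have three feature sets".
- **Figure 2 legend.** In step C, for each individual, "three feature sets (lesion features, connectome features, and combination features) will be generated from the corresponding features after feature selection". The training and test cohorts first appear in step D.
- **Development and Validation of Prediction Models.** Before the split is described: "All the variables will be centered and standardized before being entered into each model". After Figure 2: "Images from four sites (four hospitals) will be randomly partitioned into four equal portions", with about three quarters for training and one quarter for test. The univariate P < 0.05 screen against the outcome is expressly run in the training cohort. Final accuracy is defined on the test cohort, and the Abstract calls this external validation.

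**The concern.** A test cohort is informative because nothing about the fitted model was learned from it. Here the feature lists, and probably the hospital means and variances, would be estimated with the test children included. The one step that the authors clearly confine to the training cohort is the outcome-based screen.

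The primary aim is to develop and validate a model for individual children, and the test cohort is the only evidence offered for the validation half. If pre-processing has already seen those children, the reported figure does not describe a frozen model applied to a newly diagnosed child. The size and direction of any error would depend on settings that the text does not give.

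**Working it through.** **1. Which children each step covers, as written**

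| Step | Children covered | Uses outcome? |
|---|---|---|
| ComBat | the data; no limit, timing not stated | not stated |
| 10% and 75% filters | the patients; ends with feature sets for each subject | no |
| Centring and scaling | not stated | no |
| Split into training and test | all images, described after the steps above | no |
| P < 0.05 screen | training cohort, expressly | yes |
| Final accuracy | test cohort | for scoring only |

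The filters read as covering everyone. ComBat reads that way by contrast with the screen. Scaling is open.

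**2. Cohort sizes**

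The plan's figure is: "If α = 0.05, 1-β = 0.80, then the study requires enrollment of 143 participants", with f² = 0.10 and "the number of predictors was set as 6". A noncentral F test with 6 and N − 7 degrees of freedom and noncentrality 0.10 × N gives power 0.801 at N = 143, so the figure reproduces. For 20% dropout, 143/0.80 = 178.75 (stated as 178; the rounding does not matter here).

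The split gives 143 × 0.75 = 107.25 training and 35.75 test children, about 107 and 36. With four hospitals of equal size (an assumption), each has about 143/4 ≈ 36 children: 107/4 ≈ 27 training and 9 test.

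**3. Why a step that ignores the outcome can still matter**

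Take plain centring of one feature in one hospital on all 36 children, and let m_tr and m_te be the training and test means after centring:

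27 × m_tr + 9 × m_te = 0, so m_te = −3 × m_tr.

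Any hospital-level deviation left in training is reversed, three times as large, in test. If hospitals differ in impairment rate, the training screen favours features whose leftover hospital means line up with those rates, and these then point the wrong way in test. If rates are equal, hospital says nothing about outcome and the reversal costs nothing. Centring on training children alone gives m_tr = 0, so there is nothing for the screen to pick up. ComBat's empirical Bayes shrinkage softens the exact identity.

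**4. Simulated test AUC, pooled versus training-only fitting (N = 143)**

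Both sets use four hospitals, a 107/36 split, 2,000 features, a training-only P < 0.05 screen, a ridge classifier and 200 runs per setting. Set A has correlated features, site-shift SD 0.3 and empirical Bayes ComBat. Set B has independent features, site-shift SD 0.7 and location/scale adjustment without shrinkage, and also switches the 75% filter between pooled and training-only fitting. All of these settings are assumptions.

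| Set | Hospital rates | Signal | Pooled | Training-only | Difference |
|---|---|---|---|---|---|
| A | equal | no | 0.49 | 0.49 | 0.00 |
| A | equal | yes | 0.948 | 0.951 | −0.003 |
| A | 40–60% | yes | 0.934 | 0.948 | −0.014 |
| A | 46–78% | no | 0.47 | 0.49 | −0.02 |
| A | 46–78% | yes | 0.900 | 0.930 | −0.030 |
| A | 30–80% | no | 0.46 | 0.51 | −0.05 |
| B | equal | no | 0.503 | 0.503 | 0.000 |
| B | equal | yes | 0.658 | 0.646 | +0.012 |
| B | 30/45/60/75% | no | 0.430 | 0.491 | −0.061 |
| B | 30/45/60/75% | yes | 0.540 | 0.636 | −0.096 |

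The standard error of the paired difference in A is 0.001–0.004. In B each mean has a standard error of 0.006–0.008. The +0.012 in B becomes 0.680 − 0.693 = −0.013 at N = 178, so it is noise. A further location/scale run gave a change under 0.01 with equal rates, about −0.02 at 46–78% and about −0.05 at 30–80%.

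The equal-rate settings in B pool the filter and the scaling as well and show no visible effect. Neither step involves hospital, so ComBat is the likely driver.

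**5. If CFCS group were preserved in a pooled ComBat fit**

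On pure noise, A gives AUC 0.53–0.61. B gives 0.609 with unequal rates and 0.508 with equal rates.

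**6. Scale**

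The 95% half-width of a test accuracy runs from 1.96 × √(0.8 × 0.2/45) = 0.117 to 1.96 × √(0.7 × 0.3/36) = 0.150.

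**The case against.** The case against is substantial. Section order is not execution order. The Harmonization section gives no timing, and the Figure 2 legend mentions neither ComBat nor scaling. Step C speaks of feature selection although one selection step runs inside the training cohort, so the lettering may be schematic. The scaling sentence is compatible with training-only constants. No step is described as using test outcomes. Any effect needs impairment rates that differ by hospital; the 46–78% in the Introduction is a range across published studies, not across these four hospitals. The resulting bias is mainly downward, which would make the validation claim conservative, and it is small beside the sampling error. Scanner field strength, make and acquisition parameters are also to be the same at all sites.

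Most of this stands, and it limits the point. It does not remove it. The filters are printed as covering the patients and yielding feature sets for each subject before the split. The authors restrict a step to training when they mean to, and they do not do so for the filters or ComBat. Matching scanners do not help much, because the reversal in step 3 comes from sampling error in the hospital means rather than from true scanner differences. A conservative but avoidable error is still an error in the key figure.

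**Conclusion.** The point holds in a limited form. On the natural reading, the test cohort is not held out from the prevalence filters or from ComBat, and for scaling the text does not settle the matter. The test figure would then not describe a locked model.

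The effect is negligible if hospitals have similar impairment rates. If they differ, test AUC can fall by about 0.02 to 0.05 in most settings tried. It fell less with rates of 40–60% and by as much as 0.10 without shrinkage. These sizes rest on assumed hospital rates and simulation settings.

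A reader might infer more: that test accuracy is definitely biased or inflated, that test outcomes enter the model, or that scaling is stated to precede the split. The documents support none of these. The only outcome-based screen is confined to training, the direction without outcome covariates is downward, and inflation would need CFCS group as a ComBat covariate, which the text does not say.

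**What to change.** State in Harmonization, in Preselection of Predictive Features, in Development and Validation of Prediction Models and in Figure 2 that the split comes first. Estimate the ComBat site parameters, the 10% and 75% feature lists and the centring and scaling constants in the training cohort only, and within the training folds during cross-validation. Apply them unchanged to the held-out children. List the ComBat covariates and leave CFCS out.

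The cost is two or three sentences and a change in code order. No new data are needed and the sample size stays at 143/178. The small downside is precision: with hospitals of equal size, site parameters rest on about 27 rather than 36 children each, and on about 27 × 0.9 ≈ 24 within cross-validation folds. The frozen site parameters cover only the four participating hospitals, so this does not by itself show performance at a new one.
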